**Methods/design:**

This is a single blind, parallel-group, randomised controlled trial with blinded assessment of outcome and intention-to-treat analysis. LTC residents (age ≥ 65 years) will be recruited from LTC facilities in New Zealand. Participants (*n* = 528 total, with a 1:1 allocation ratio) will be randomly assigned to either a novel exercise program *(Staying UpRight)*, comprising strength and balance exercises designed specifically for LTC and acceptable to people with dementia (intervention group), or a seated exercise program (control group). The intervention and control group classes will be delivered for 1 h twice weekly over 1 year. The primary outcome is rate of falls (per 1000 person years) within the intervention period.

Secondary outcomes will be risk of falling (the proportion of fallers per group), fall rate relative to activity exposure, hospitalisation for fall-related injury, change in gait variability, volume and patterns of ambulatory activity and change in physical performance assessed at baseline and after 6 and 12 months. Cost-effectiveness will be examined using intervention and health service costs.

The trial commenced recruitment on 30 November 2018.

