### Assessments

Demographic and health information (health conditions, medications, independence in activities of daily living) will be collected using a standardised Minimum Data Set (MDS 2.0; interRAI Corporation 1999) at baseline prior to randomisation. The interRAI™ (International Resident Assessment Instrument) Long-Term Care Facilities (LTCF) assessment is a standardised comprehensive observational assessment, completed on admission and 6-monthly thereafter by nursing staff for all residents in LTC.

Cognitive function will be measured at baseline and at 6 and 12 months using the Montreal Cognitive Assessment (MoCA) [34]. The MoCA comprises 16 items to assess multiple cognitive domains. A score of ≤ 10/30 is considered severe cognitive impairment, 11–18 moderate impairment, 19–23 mild and > 23/30 normal cognitive function [35].

Ambulatory activity over 7 days will be collected using the tri-axial accelerometer and data uploaded to an encrypted, secure platform (eScience Central online platform, Newcastle University, UK) [36] for storage and blinded processing.

Outcome measures will be completed at baseline and at 6 and 12 months (Fig. 2). Assessors will be trained in all aspects of participant assessment, activity monitoring and digital data management to ensure the assessments are standardised. Assessors will watch a standard assessment and each will rate the responses. Responses will be compared and discussed.

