### Sample size estimation

The sample size is estimated on the primary outcome, fall rate. To detect a 25% reduction in falls, assuming a control rate of 2.6 falls per resident per year (based on pilot data), we estimate a required sample size of 264 in each group (*n* = 528; two-tailed test, a = 0.05, power = 90%). The anticipated drop-out rate is 35%, which will be replaced by recruitment at participating facilities throughout the trial. Final recruitment will stop 12 weeks prior to completion of the 12-month intervention in each facility.

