### Statistical analysis

The primary analysis will be conducted on an intention-to-treat basis using data from all randomised participants, although a ‘per protocol’ analysis of the primary outcome will also be reported.

Total number of falls, number of fallers, people sustaining a fall-related fracture or brain injury; fall rate (falls per 1000 person years); multiple fallers and number in each analysis will be reported. Prior fall-incidence rates will be calculated as number of falls/resident/year using the audited 6 months prior to enrolment.

Negative binomial regression models will be fitted to determine the incidence rate ratio (IRR) for differences in fall rates between groups both for overall follow-up time as the primary endpoint and secondarily as activity-adjusted rates. Similar negative binomial models will be built for fall injury rates; fractures and head injuries both combined and separately. Logistic regression models for fallen during follow-up or not fallen and for having fallen multiple times during follow-up or not fallen will be compared between the intervention and control groups.

All models will control for prior fall rate, level of dependency and cognition (MoCA), as these are confounding factors. Baseline data will be compared between the two groups, with any strongly imbalanced factors further adjusted for in the analysis.

Per protocol analyses will be performed including those with higher attendance, and pre-planned subgroup analyses will include those with moderate and high levels of cognitive impairment.

Fall rate relative to activity exposure will be calculated and compared between groups. Within-group change will be examined using repeated measures. Generalised linear mixed-effects regression models will be used for volume, pattern and variability of ambulatory activity and cognition.

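### The covariate rule for all models does not bring in the baseline value of the ambulatory-activity outcomes by default, and the role of their baseline visit is left open

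*Protocol article*

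**What the plan says.** The Statistical analysis section of the protocol article sets one covariate list: "All models will control for prior fall rate, level of dependency and cognition (MoCA), as these are confounding factors". The next sentence gives the only stated route for further covariates: "Baseline data will be compared between the two groups, with any strongly imbalanced factors further adjusted for in the analysis".

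The same section later assigns the model family: "Generalised linear mixed-effects regression models will be used for volume, pattern and variability of ambulatory activity and cognition". On the time course it adds: "Within-group change will be examined using repeated measures".

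The Assessments section gives the visits: "Outcome measures will be completed at baseline and at 6 and 12 months". The Randomisation section places allocation after the baseline assessment, so the baseline activity week is a pre-randomisation measurement. The Background section makes a rise in the volume of walking activity, and a change in its pattern, a secondary hypothesis.

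The article does not say whether the baseline visit is a covariate, a response or unused in the mixed models, nor which contrast is the group comparison.

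**The concern.** The list suits the falls models, which get their own baseline through prior fall rate. Cognition gets its own through MoCA. The activity outcomes do not get theirs. The same measure at baseline would usually be expected to predict a resident's 6- or 12-month value well, yet under the stated rule it becomes a covariate only if the arms happen to differ strongly on it.

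That is a poor trigger. Adjustment for a prognostic baseline value reduces variance in proportion to its squared correlation with the outcome, whether or not the arms are balanced on it. A rule tied to observed imbalance secures the gain only by accident and makes the model depend on the data. At stake is the precision with which the secondary hypothesis about activity is tested.

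**Working it through.** **Stated figures.** The article gives no sample size, power or precision for the activity outcomes, so there is no figure on this point to reproduce. The 264 per group in Sample size estimation is for fall rate: "To detect a 25% reduction in falls, assuming a control rate of 2.6 falls per resident per year (based on pilot data". With rates 2.6 and 2.6 × 0.75 = 1.95, two-sided 5% and 90% power, the log rate-ratio formula n = (z_α/2 + z_β)²(1/2.6 + 1/1.95 + 2k)/ln(0.75)² gives 114 with k = 0 and 264 with a dispersion k of about 0.59. The article does not state k, so 264 can be neither confirmed nor refuted. It does not bear on this point beyond supplying a number per arm.

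**Inputs.** Visits at baseline, 6 and 12 months (Assessments); covariate list and imbalance rule (Statistical analysis); 264 per arm (Sample size estimation). *Assumption:* r, the correlation between baseline and follow-up that remains after the listed covariates, is 0.5 to 0.8. The document gives no value. The formulas also assume equal variances at the visits and an approximately normal outcome.

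**Formulas.** Variance of the estimated 12-month group difference, in units of 2σ²/n:

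- baseline unused, or the plain 12-month difference from a model with separate arm means at every visit: 1
- difference in change, arm means at baseline unconstrained: 2(1 − r)
- baseline as covariate, or as a response with a common baseline mean: 1 − r²

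The standard-error ratio to the last option is √[1/(1 − r²)] if baseline is unused and √[2(1 − r)/(1 − r²)] = √[2/(1 + r)] for change.

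| r | Unused | Change | Adjusted | SE ratio, unused | SE ratio, change |
|---|---|---|---|---|---|
| 0.5 | 1.00 | 1.00 | 0.75 | 1.155 | 1.155 |
| 0.7 | 1.00 | 0.60 | 0.51 | 1.400 | 1.085 |
| 0.8 | 1.00 | 0.40 | 0.36 | 1.667 | 1.054 |

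Below this range the order of the two losses reverses: at r = 0.3 the SE ratios are 1.048 (unused) and 1.240 (change).

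**Checks at r = 0.7.** Generalised least squares with three visits gave 1.00 for the plain 12-month difference, 0.60 for the change contrast and 0.51 with a common baseline mean. A simulation of 3,000 trials gave 1.00 (follow-up only), 0.61 (change) and 0.52 (baseline as covariate).

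**Detectable difference.** At 80% power (my choice), (1.960 + 0.842)√(2v/n) with n = 264 and r = 0.7 gives:

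- unused (v = 1): 0.244 SD
- change (v = 0.60): 0.189 SD
- adjusted (v = 0.51): 0.174 SD

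With 171 per arm (about 65% of 264, if the anticipated 35% drop-out left that many at 12 months) these become 0.303, 0.235 and 0.216 SD. The article says drop-outs will be replaced, so the actual number is unknown.

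**The case against.** The strongest reply is that the loss may not occur. Outcomes are measured at three visits, the section names repeated measures and mixed models, and the abstract words some secondary outcomes as change ("change in physical performance assessed at baseline and after 6 and 12 months"). On a natural reading the baseline visit is already a response. With a common baseline mean nothing is lost, and with an unconstrained change contrast the loss is modest. Which of these applies is the kind of detail that an article leaves to the analysis plan. This stands: a reader might infer from the covariate list that the activity comparisons are certainly less precise than the data allow, and the document does not support that.

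It can also be said that the list is a minimum, and that its sentence follows directly on the falls models and may have been meant for them. That is possible, but the wording covers every model, and the only stated way in for another covariate is marked imbalance. This is a stated rule rather than a gap, so the point survives in limited form.

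A second tempting inference concerns cognition. MoCA is both a listed covariate and a modelled outcome. If baseline MoCA were used on both sides of a random-intercept model with equal correlations of 0.7, its slope would be (1 + 2 × 0.7)/3 = 0.8. The true follow-up residual variance would be 1 − 2(0.8)(0.7) + 0.8² = 0.52, against a pooled model variance of (0.04 + 0.52 + 0.52)/3 = 0.36. The effective critical value would be 1.96√(0.36/0.52) = 1.63, or about 10% type I error for the adjusted 12-month difference. In the same model, however, the average residual covariance is (−0.02 − 0.02 + 0.22)/3 = 0.06, so the within-person variance is 0.36 − 0.06 = 0.30. The change contrast then has model variance 2 × 0.30 = 0.60, equal to its true value 2(1 − 0.7) = 0.60, and is nominal. The inflation needs a combination of choices that the article nowhere makes, so it is not demonstrated.

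**Conclusion.** The point holds as one of efficiency. By default the stated rule leaves the pre-randomisation value of the activity outcomes out of the covariates, and the imbalance trigger does not secure the gain from using it. The size depends on the unstated role of the baseline visit. At an assumed r of 0.5 to 0.8 the standard error, relative to baseline adjustment, is about 15% to 67% larger if baseline is unused, about 5% to 15% larger for an unconstrained difference in change, and no larger with a common baseline mean.

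The scope is the outcomes named in the mixed-model sentence. The other micro-gait domains (pace, rhythm, asymmetry, postural control) have no model named in the article, so the point should not be extended to every gait outcome. There is no bias in the group comparison. The primary analysis, which already adjusts for prior fall rate, is not affected.

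**What to change.** Amend the Statistical analysis section so that, for the activity outcomes in the mixed models, the baseline value of the same outcome always enters, whatever the observed imbalance, in addition to the listed covariates. Either form will do:

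- the 6- and 12-month values are the responses, baseline is a covariate, and the group contrast is taken at each visit; or
- all three visits are responses, with the arms constrained to a common baseline mean.

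The second form also keeps residents whose baseline accelerometry is missing. The first drops them unless missing baselines are handled. For cognition, state that baseline MoCA is either a covariate or a response, not both; this is a clarification.

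The cost is a sentence or two of wording and the choice between the two forms, made before unblinded data are seen. No new data are needed.

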#### Intervention group

Participants randomised to the intervention group will attend the *Staying UpRight* program. *Staying UpRight* is a supervised balance and strength group exercise program (up to eight per group) delivered for 1 h twice weekly over 1 year. Classes will be led by a physiotherapist trained in programme delivery, supported by an assistant. Balance exercises comprise static and dynamic activities progressed by reducing hand support, reducing the base of support, reducing visual input or adding a cognitive task. The strength exercises use body weight resistance and low repetitions (2 × 10 repetitions at 5–7/10 effort) in weight-bearing positions where possible (Table 1). Exercises are progressed by increasing the number of sets, the speed or amplitude of the movement or the complexity of the task (Table 2). The programme is manualised, with exercises and progressions selected based on participants’ abilities. Exercises completed in each session and exercise progressions for the group will be recorded on a spreadsheet and reviewed as part of fidelity monitoring.

**Table 1 Tab1:** *Staying UpRight* exercises and progression principles

STRENGTH EXERCISES	
*Progression principles*	
Increase duration of static hold; increase repetition; increase number of sets; alter speed, distance moved, reduce hand support, move from sit to stand, decrease base of support (BoS)	
*Lower limb*	*Description*
Hip extension; abduction, flexion	- Stand up straight, engage core. Lower leg to floor after each movement
Lunges	- Step forwards or sideways. Bend both knees and sink towards floor. Push up with both legs to return. Repeat with alternate leg initiating step
Squats	- Standing behind chair, feet shoulder width apart, bend both knees and sink to the floor. Push up into standing. Progress by reducing hand support, increasing depth of squat, increasing speed
Sit to stand	- Standing up from chair. Progress by reducing hand support, increasing speed
Heel raises and toe raises	- Standing behind chair, lifting heels off the floor. Lifting toes off the floor.
*Upper limb*	
Breaststroke	- Hands together in front of chest. Push arms forward, pull to side & back as if doing breaststroke
Shoulder press	- Hands at shoulder level, elevating arms to ceiling through flexion. Progress from seated to standing, increase speed
Biceps curl	- Elbow flexion

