#### Control group

Control group participants will attend a seated group activity programme (*Flex and Stretch*) delivered for 1 h twice weekly over 1 year. Classes are led by the LTC activities staff or a volunteer trained in programme delivery. Activities comprise lower limb, trunk, upper limb, head and neck movements without resistance or progressions, e.g. seated swimming, boxing, seated marching, heel and toe tapping and seated stretches; as well as activities, e.g. balloon catch and throw, pass the parcel. The programme is manualised, with class duration for each session recorded.

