### Contamination

Contamination between intervention and control groups is best controlled by a cluster randomised design, but that also introduces considerable heterogeneity given differences in length of stay, spatial design of the LTC and differences in staffing ratios. Fall rates in facilities in a previous trial varied from 0.68 fall per resident year to 7.67 falls per resident year [37]. LTC facility factors found to be associated with falls included the level of care (low-level dependency had the highest rate of falls) and staffing ratios [5]. Individualised randomisation addresses these issues, although it introduces the possibility of contamination. Contamination between intervention and control groups will be managed by separating delivery of the intervention and control classes, maintaining attendance registers for intervention and control classes and using different facilitators for intervention and control groups.

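### The per-protocol analysis of fall rate selects on attendance, which a fall can reduce and probably more so in the weight-bearing arm, so it is likely to lean towards the intervention

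*Protocol article*

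**What the plan says.** The hierarchy is clear in the protocol article, Statistical analysis: "The primary analysis will be conducted on an intention-to-treat basis using data from all randomised participants". Next to it, a per-protocol "analysis of the primary outcome will also be reported". The same section gives the only rule for who enters that set: "Per protocol analyses will be performed including those with higher attendance".

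On adjustment it says: "All models will control for prior fall rate, level of dependency and cognition (MoCA), as these are confounding factors". All three are baseline quantities.

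The two classes differ in physical demand. Under Intervention group, strength work is done "in weight-bearing positions where possible", alongside progressive balance training. Under Control group: "Control group participants will attend a seated group activity programme", and "Activities comprise lower limb, trunk, upper limb, head and neck movements without resistance or progressions". Both run twice weekly for a year. The Primary outcome section counts falls over the 12 months of the study. Class attendance says that attendance and the reasons for nonattendance are documented in both arms.

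**The concern.** Membership of the per-protocol set is decided after randomisation, by a variable that the outcome can change. A resident who is hurt, frightened or weakened by a fall may stop coming to class, fail the attendance rule and take that fall out of the analysis. If this happened equally in both arms, the comparison would stay fair. It may not: a seated class is easier to continue after a fall than a class with standing balance work. More fallers would then leave the intervention arm's set, and its fall rate would look lower even if the programme did nothing.

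The problem lies in the principle and not in a missing cut-off. A cut-off chosen later on accumulated attendance inherits it, and baseline covariates cannot fully remove selection caused by falls during follow-up. At stake is how far a reported secondary reading of the primary outcome can be believed. Pilot attendance was 60% (Background), so any attendance rule will set aside many residents.

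**Working it through.** The plan gives no figure for the per-protocol set, so there is none to reproduce. The check asks what the rule returns when the programme has no effect.

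**Inputs from the article**
- Control fall rate: 2.6 per resident-year (Sample size estimation).
- Mean attendance: 60% (pilot, Background).
- Prior falls: a 6-month audit (Primary outcome), so a mean of 2.6/2 = 1.3.
- Only injury anchor: 5% of residents with a fracture yearly (Background). Per fall this is 0.05/2.6 = 1.9%, about 2%.

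**Dispersion.** None is printed. With rates 2.6 and 2.6 × 0.75 = 1.95, two-sided alpha 0.05 and 90% power, the negative binomial formula is

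n = (1.960 + 1.282)² × (1/2.6 + 1/1.95 + 2k) / (ln 0.75)².

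At k = 0 it gives 114 per group. It gives the stated 264 at k = 0.59. Both k = 0.59 and k = 1 are used below.

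**Assumptions.** Falls are Poisson given a gamma frailty, and the prior count shares that frailty. Attendance before any stopping is Beta with mean 0.60 (two spreads tried). Each fall permanently ends attendance with an arm-specific probability, at a uniform time in the year. The rule is applied to both arms, which the article does not specify. There are 200,000 residents per arm and the true rate ratio is 1. The adjusted column is a negative binomial model with the prior fall count; dependency and MoCA are not simulated.

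**Results at a 50% attendance cut-off** (range over both k and both spreads)

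| Falls ending attendance, intervention vs control | Crude rate ratio | Adjusted for prior falls | Mean intervention attendance |
|---|---|---|---|
| 10% vs 10% | 0.99-1.00 | 0.99-1.00 | 0.53 |
| 2% vs 1% | 0.97-0.99 | 0.98-0.99 | 0.59 |
| 5% vs 2% | 0.92-0.95 | 0.95-0.96 | 0.56 |
| 10% vs 5% | 0.88-0.92 | 0.92-0.94 | 0.53 |
| 15% vs 5% | 0.79-0.84 | 0.85-0.88 | 0.51 |
| 20% vs 10% | 0.79-0.85 | 0.85-0.88 | 0.48 |

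Intention-to-treat stays at 1.00 within simulation error throughout. With equal stopping there is no bias, so the difference between arms drives the result.

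**Sensitivity**
- Cut-off: with 8% vs 4% of falls ending attendance (10% injurious, of which 0.8 vs 0.4 stop) and k = 0.59, the crude ratio runs only from 0.94 at a 40% cut-off to 0.92 at 70%.
- Duration: in that scenario at a 50% cut-off, the crude ratio is 0.93 if stopping is permanent and 0.96 if each such fall interrupts attendance for 12 weeks.
- False benefit: with 264 per arm in that scenario and no covariate adjustment, a significant benefit appears in 10% of trials if stopping is permanent and 6.4% if it lasts 12 weeks (nominal 2.5%).

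**The case against.** The strongest reply is that the key premise is not documented. Nowhere does the article say that a fall stops attendance more readily at Staying UpRight. Exercises are chosen to fit each participant's abilities, a physiotherapist leads the classes at first with an assistant, and Table 1 includes seated starts and chair support. A resident who has fallen could be stepped back within the class. This stands: the difference between arms, and even its direction, is inferred from the class descriptions.

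A reader might infer that the bias could match the 25% reduction the trial seeks. It does not under the planned adjustment. Crude ratios below 0.80 need 15-20% of falls to end attendance for good. Those scenarios pull intervention attendance down to about 0.48-0.51, although the pilot's 60% already includes any fall-related stopping. Adjusting for prior falls then moves the ratio to 0.85-0.88, and to 0.83 at worst with a 70% cut-off. The simulation treats frailty as constant over time, so it may flatter the adjustment somewhat.

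A reader might also infer that controls who went to Staying UpRight classes stay in the per-protocol set. The article does not say so. The Contamination section plans on "maintaining attendance registers for intervention and control classes", and detailed membership criteria may sit in an analysis plan that is not shown. The absent cut-off is no finding for the same reason.

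Finally, the per-protocol result is secondary, and nothing in the article lets it carry the efficacy claim. That limits the consequence but does not make the rule sound.

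**Conclusion.** The point holds in a limited form. The stated rule conditions on a variable that accrues while the outcome accrues and that the outcome can change. The two classes differ in a way that makes unequal loss of fallers likely, in the direction that favours the intervention.

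With no true effect and adjustment for prior falls, the expected distortion is about 1-2% if only falls as serious as fractures end attendance. It is about 4-8% (rate ratio 0.92-0.96, 50% cut-off) if 5-10% of falls do so in the intervention arm and half that or less in control. These figures rest on assumed stopping probabilities, permanent stopping and the same filter in both arms; shorter interruptions shrink them. The primary intention-to-treat result is not touched.

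**What to change.** Replace, or at least accompany, the attendance-selected analysis with a complier average causal effect estimate on all randomised participants. Use randomisation as the instrument and recorded attendance at Staying UpRight, including any by controls, as the exposure. It rests on the randomised contrast, so fall-driven absence cannot create an effect where none exists. State the exclusion restriction openly: assignment must affect falls only through Staying UpRight attendance, which needs argument when the comparator is itself a class with its own attendance. Label the result supportive.

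If an attendance-selected set is still reported, do not count absence recorded as due to a fall or injury as low attendance. The reasons are already collected. This reduces the problem but will miss fear or decline that is recorded under another reason.

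Two other remedies are weaker. Classifying attendance over the first 12 weeks and counting falls afterwards would leave the last replacement recruits no countable follow-up, because recruitment closes 12 weeks before each facility finishes. Dropping controls who attended the other class is a further post-randomisation exclusion.

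The cost is a wider interval and a little more programming; no new data are needed.
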